## Abstract

**Background:**

Awareness of preferences regarding medical care should be a central component of the care of patients with advanced cancer. Open communication can facilitate this but can occur in an ad hoc or variable manner. Advance care planning (ACP) is a formalized process of communication between patients, relatives and professional caregivers about patients’ values and care preferences. It raises awareness of the need to anticipate possible future deterioration of health. ACP has the potential to improve current and future healthcare decision-making, provide patients with a sense of control, and improve their quality of life.

**Methods/Design:**

We will study the effects of the ACP program Respecting Choices on the quality of life of patients with advanced lung or colorectal cancer. In a phase III multicenter cluster randomised controlled trial, 22 hospitals in 6 countries will be randomised. In the intervention sites, patients will be offered interviews with a trained facilitator. In the control sites, patients will receive care as usual. In total, 1360 patients will be included. All participating patients will be asked to complete questionnaires at inclusion, and again after 2.5 and 4.5 months. If a patient dies within a year after inclusion, a relative will be asked to complete a questionnaire on end-of-life care. Use of medical care will be assessed by checking medical files. The primary endpoint is patients’ quality of life at 2.5 months post-inclusion. Secondary endpoints are the extent to which care as received is aligned with patients’ preferences, patients’ evaluation of decision-making processes, quality of end-of-life care and cost-effectiveness of the intervention. A complementary qualitative study will be carried out to explore the lived experience of engagement with the Respecting Choices program from the perspectives of patients, their Personal Representatives, healthcare providers and facilitators.

**Discussion:**

Transferring the concept of ACP from care of the elderly to patients with advanced cancer, who on average are younger and retain their mental capacity for a larger part of their disease trajectory, is an important next step in an era of increased focus on patient centered healthcare and shared decision-making.

**Trial registration:**

International Standard Randomised Controlled Trial Number: ISRCTN63110516. Date of registration: 10/3/2014.

## Background

Despite progress in diagnosis and treatment, cancer remains a major life limiting disease, with 14.1 million new cases and 8.2 million deaths worldwide in 2012 [1]. Patients with advanced cancer typically suffer from a reduced quality of life and multiple symptoms, such as pain, fatigue, and dyspnoea, due to their illness and/or its treatment [2]. A diagnosis of advanced cancer often has a tremendous impact on patients’ emotional wellbeing and may result in depression, anxiety and a feeling of loss of control [3, 4]. Ideally, these patients receive patient-centered care, addressing their needs concerning symptom control, psychosocial support, spiritual support, and practical issues. Patients’ preferences regarding care and their wishes concerning their place of residence at the end of life should be central in the decision-making. Currently, treatment aimed at prolonging life has been found to often prevail over care aimed at relieving patients’ suffering and enhancing their quality of life, which may not always be in accordance with patients’ needs and preferences [5].

Timely and efficient communication is an important prerequisite for care that adequately addresses patients’ needs and preferences [6]. However, research findings consistently demonstrate that communication between physicians, patients with advanced cancer and their relatives is complex. Physicians tend to focus on treatment [7], patients may be overwhelmed and unaware of the possibility to opt for treatment aimed at relieving suffering, and relatives may feel stressed and uncertain to be involved in medical decisions without being aware of their beloved one’s preferences [8].

Advance care planning has moved from being a process which aims to elicit specific instructions about medical treatment at the end of life, to being recognized as an opportunity to help patients and their families to prepare, in their own terms, for the changes wrought by serious progressive illness and work with them to plan nursing, social and medical care so that it better fits their needs, hopes and aspirations [9]. ACP is a formalized process of communication between patients, relatives and professional caregivers. It has been defined as “a voluntary process of discussion about future care between an individual and their care providers, irrespective of discipline. […] It is recommended that with the individual’s agreement this discussion is documented, regularly reviewed, and communicated to key persons involved in their care” [10]. ACP promotes discussion of preferences and communication of these preferences to family, friends and healthcare professionals. Patients are encouraged to document their preferences in an advance directive and to review these preferences as circumstances change. Patients are also encouraged to appoint a personal representative, who can express their preferences if they are unable to do so themselves. However, the legal status of advance directives and personal representatives differs across countries. A review of the literature [11] shows that ACP programs have the potential to improve communication between patients and healthcare professionals, increase the quality of life and well-being of patients and their relatives, reduce the use of futile treatments and unnecessary hospitalisations, enhance provision of care that is consistent with patient goals, and increase patients’ satisfaction with care. Other studies have shown that ACP can reduce healthcare costs [12–14]. The Respecting Choices program is one of the most promising ACP program. This program was developed in the US and successfully trialed in a geriatric setting in Australia, showing that patients’ end of life care wishes were much more likely to be known and followed in the intervention group (86 %) compared to the control group (30 %).

Most ACP studies have been performed in the US, amongst nursing home patients with the main aim of establishing patients’ preferences before they lose their competence. We will conduct our study in a European context and hypothesize that ACP can also be effective in improving the quality of life of patients with cancer who often remain competent until death or very close to death. ACP may support them in timely recognizing and continuously expressing their core values and preferences, and to communicate these with their loved ones and professional care givers, which will enable strategic and effective planning of care and decision-making. As a result, care may more adequately address patients’ values and preferences, which may result in improved quality of life and more adequate symptom control, while patients feel more in control and receive less unwanted or futile interventions.

The overall hypothesis that will be studied in the ACTION project is that a formalized ACP program such as Respecting Choices significantly improves the quality of life and reduces the symptom burden of patients with advanced lung or colorectal cancer.

The primary objective is to assess the effect of the Respecting Choices ACP program on the quality of life and symptoms of patients with advanced lung or colorectal cancer.

The secondary objectives are:To assess the effect of the Respecting Choices ACP program on the quality of life and symptoms of patients with advanced cancer in different subgroups (gender, age, education, ethnicity, country and type of cancer).To assess the effect of the Respecting Choices ACP program on the extent to which care as received is in line with patients’ documented preferences, on patients’ evaluation of the quality of the decision-making process, and on how they cope with their illness.To assess patient satisfaction with the Respecting Choices ACP program.To assess the effect of the Respecting Choices ACP program on the quality of end of life care of patients with advanced cancer from the bereaved carers’ perspective, and on the wellbeing of these carers.To assess the cost effectiveness of the Respecting Choices ACP program.To gain insight into how patients, patients’ relatives and professional caregivers experience and respond to facilitated ACP.

## Methods/design

### Study design and setting

We will perform a multicenter cluster-randomised clinical trial in 22 hospitals in six European countries (Belgium, Denmark, Italy, the Netherlands, Slovenia and the United Kingdom). Per country pairs of comparable hospitals (academic/non-academic) will be randomised to provide either ‘care as usual’ supplemented with ACP or ‘care as usual’. Cluster-randomisation prevents healthcare providers from giving patients in the control group (‘care as usual’) more opportunity to discuss their preferences than usual due to their experience with providing the intervention in the intervention group (‘care as usual’ supplemented with ACP). The nature of the intervention makes blinding, for both healthcare professionals and patients and their relatives, impossible.

### Study population

In total, 1,360 patients with advanced lung (*N* = 680) or colorectal cancer (*N* = 680) will be included. Lung and colorectal cancer patients are selected for this study because both types of cancer have high incidence and mortality rates in Europe and affect both sexes; see Table 1 for in- and exclusion criteria. At inclusion, the average life expectancy of these patients is about one year; their minimum estimated life expectancy to be eligible for the study is three months.

**Table 1 Tab1:** Inclusion and exclusion criteria

Inclusion criteria	Exclusion criteria
Histologically confirmed diagnosis of: • Lung cancer:	Age < 18 years
- small cell - extensive disease/Stage III or IV* - non-small cell - stage III or IV*	Unable to provide consent
• Colorectal cancer: Stage IV or metachronous metastases*	Unable to complete questionnaire in country’s language
*according to 7th edition of TNM classification and staging system	Less than 3 months anticipated life expectancy
Written informed consent to participate	Taking part in a research study that is evaluating palliative care services or communication strategies.
WHO performance status of 0–3.	

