Patients will be followed until one year after inclusion. During the inclusion period eligible patients in both intervention and control hospitals, will be approached for written informed consent. The information provided in the consent form for the intervention group and the control group will be as similar as possible to avoid selection bias with respect to interest in ACP. However, to minimize contamination, patients will be informed that the project aims at investigating the experiences of patients with different approaches towards medical decision-making in advanced stages of cancer, but no or limited details of the Respecting Choices program will be revealed in the control group. Patients will be given ample time to consider participation and they are free to withdraw from participating in the study without any effect on their care.

Patients in the intervention group will be offered the Respecting Choices program in addition to their usual care. Depending on the health status of the patient and the content of the conversations, a facilitated interview will last 45–60 min on average. We plan to have one or two sessions per patient. The facilitator will assist the patient in documenting preferences, including the assignment of a personal representative. For quality assurance, the interviews will be audio recorded by the facilitator.

By a standardized checklist a proportion of the interviews will be rated for intervention fidelity [16].

Ethical committee procedures have been followed in all countries and institutions involved, and approval has been provided. The names of the main IRB’s are:The Netherlands: Medische Ethische Toetsings Commissie (METC) ErasmusMC;Belgium: Universitair Ziekenhuis Brussel Commissie Medische Ethiek;United Kingdom: NRES Committee North West - Liverpool East;Italy: Comitato Etico Area Vasta Centro, Regione Toscana;Denmark: De Videnskabsetiske Komiteer for Region Hovedstaden;Slovenia: Komisija Republike Slovenije za medicinsko etiko (KME).

Approval was also obtained from the IRB’s of all the remaining institutions.

The trial is registered in the International Standard Randomised Controlled Trial Number (ISRCTN63110516). A Data Steering Monitoring Board (DSMB) will be established.

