### Analyses

Analyses of the primary and secondary endpoints will be performed following the intention-to-treat principle. Descriptive statistics will be used to summarize characteristics of countries, hospitals and patients. Patient characteristics (age, gender, socio-economic class, educational level) will be compared at baseline between the intervention and control group. A multilevel modelling approach will be used to examine differences in the endpoints between the intervention and control groups, taking account of clustering effects at both hospital and country-level. All statistical tests will be two-sided and considered significant if *p* < 0.05. Repeated-measures analyses of variance will be conducted to assess the development of endpoints over time.

Subgroup analysis will be conducted by means of formal interaction tests for intervention and those variables which are more likely to influence the effect of the intervention itself: gender, age class (<65, 65–74, 75+), educational status, and country.

Those conducting the data analysis will be blinded as to whether the patient was included in the intervention group or in the control group.

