In ACTION, we expect to encounter some challenges and possible limitations. First, patients may decline participation for different reasons. They may feel overwhelmed by the topics raised in the ACP intervention sessions and may not (yet) feel prepared to talk about these issues. We will use a patient-centered approach to facilitate study participation. Patients will receive information about the project through their treating specialist. Since patients may refuse because they do not want to engage in ACP conversations, non-response bias cannot be ruled out. Also selection bias cannot be ruled out, e.g. in intervention hospitals’ where including physicians may be more likely to ask patients who they think are more ‘open’ to ACP to participate in the study. If such ‘gatekeeping’ comes into play, the effect of the intervention may be overestimated. However, our approach to systematically assess all lung and colorectal cancer patients for eligibility, and subsequently invite all who are eligible to participate in the study may reduce this risk. Attrition is another potential limitation to this project. Attrition may occur because the condition of the patient might worsen such that further participation becomes impossible, or patients might die during follow-up. We try to limit attrition by adding the inclusion criterion of a minimal anticipated life-expectancy of three months and to measure our main outcome measure at 2.5 months. Third, the international character of this project might be a challenge, as a balance needs to be found between on the one hand testing a uniform intervention in the six countries, that on the other hand is tailored to the specific cultural, ethical and legal context of each country. Fourth, the extent to which actual care will be reflected in medical files can be questioned. Potentially, not all treatments that patients receive will be documented in the hospital medical files.

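### The named baseline comparison of the arms covers four sociodemographic variables only, which fits badly with the arm-specific selection that the protocol concedes

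*Protocol article*

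**What the plan says.** All references are to the protocol article.

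- **Randomisation and blinding (Study design and setting).** "Per country pairs of comparable hospitals (academic/non-academic) will be randomised to provide either" usual care with ACP or usual care alone. On blinding: "The nature of the intervention makes blinding, for both healthcare professionals and patients and their relatives, impossible".
- **Recruitment (Study procedures).** "During the inclusion period eligible patients in both intervention and control hospitals, will be approached for written informed consent". The consent information is to be as alike as possible in the two groups, but "no or limited details of the Respecting Choices program will be revealed in the control group".
- **Who may enter (Study population, Table 1).** "WHO performance status of 0–3", lung cancer of stage III or IV (or extensive small-cell disease), and metastatic colorectal cancer. The text puts average life expectancy at roughly a year and sets a floor of three months, which is an estimate and not a measurement.
- **Admitted risk (Discussion).** "Also selection bias cannot be ruled out". The example given is that physicians in intervention hospitals may favour patients they see as receptive to ACP, so that the effect would be overestimated. The stated counter-measure is to assess every lung and colorectal patient for eligibility and invite all who qualify. The text says only that this may lower the risk.
- **Baseline comparison (Analyses).** "Patient characteristics (age, gender, socio-economic class, educational level) will be compared at baseline between the intervention and control group". The same section plans an unspecified descriptive summary of countries, hospitals and patients, a multilevel model for hospital and country clustering, and repeated-measures analyses over time.
- **Baseline data (Measurements).** Quality of life and symptoms are collected at inclusion, before ACP is delivered.

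**The concern.** When hospitals are randomised and patients enrol afterwards, randomisation protects the comparison of hospitals. It does not by itself balance the patients whom each hospital goes on to enrol. Here the people who judge eligibility and approach patients are unblinded. The protocol does not say in so many words that they know the arm when they recruit, but consent information that differs by arm makes it a strong inference. One eligibility criterion, anticipated life expectancy, is a judgement.

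The protocol sees the risk and states its direction. The check that it then names uses variables with no direct bearing on prognosis or on the outcome. Two arms could agree on age, gender, social class and education and still differ in performance status, stage or starting emotional functioning. If only the named comparison were reported, a reader would have little basis for separating an effect of ACP from a difference in who was enrolled.

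**Working it through.** **1. Set the risk beside the check.**

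| Item | Where it stands | In the named baseline comparison? |
|---|---|---|
| Age, gender, socio-economic class, education | Analyses | Yes |
| WHO performance status | Table 1, needed for eligibility | No |
| Disease stage | Table 1, needed for eligibility | No |
| Baseline emotional functioning and symptoms | Measurements, collected before ACP | No |
| Tumour type | 34 + 34 per hospital (Power calculation) | No, but largely balanced by the quota |

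The list in the Analyses section stands in parentheses with no wording to mark it as examples. It is therefore a stated choice and not mere silence.

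**2. Reproduce the protocol's own power figure, to obtain the standard error.** Inputs from the Power calculation section: 11 hospitals per arm, 25 + 25 = 50 evaluable patients per hospital, ICC 0.1, target difference 0.5 SD. Two-sided 5% is from Analyses.

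- Design effect = 1 + (50 − 1) × 0.1 = 5.9.
- Effective patients per arm = 11 × 50 / 5.9 = 93.2.
- Standard error of the difference = √(2 / 93.2) = 0.146 SD.
- Target / standard error = 0.5 / 0.1465 = 3.41.
- Power = 90.1% with a t reference on 2 × 11 − 2 = 20 df, which agrees with the stated 90%. The normal approximation gives 92.7%.

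**3. Illustrate the bias.** The documents give neither a performance-status distribution nor its relation to emotional functioning, so both of the following are assumptions:

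- the difference between arms in the share of WHO 2-3 patients: 10 or 20 percentage points;
- the gap in emotional functioning between WHO 2-3 and WHO 0-1: 0.5 SD, range 0.3 to 0.8 SD.

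Bias = imbalance × gap. False-positive rate = P(Z > 1.96 − bias/SE) + P(Z < −1.96 − bias/SE), with no use of the baseline outcome.

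- 10 points: 0.10 × 0.5 = 0.05 SD; bias/SE = 0.341; rate = 0.0528 + 0.0107 = 6.3%.
- 20 points: 0.20 × 0.5 = 0.10 SD; bias/SE = 0.683; rate = 0.1008 + 0.0041 = 10.5%.

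| Imbalance | Bias at 0.5 SD gap (range) | Share of the 0.5 SD target | False-positive rate (range) |
|---|---|---|---|
| 10 points | 0.05 SD (0.03 to 0.08) | 10% (6 to 16%) | 6.3% (5.5 to 8.5%) |
| 20 points | 0.10 SD (0.06 to 0.16) | 20% (12 to 32%) | 10.5% (6.9 to 19.4%) |

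With the 20-df t reference that reproduces the stated power, the central rates are 6.2% and 10.0%, so the choice of reference changes little. Small imbalances do little harm; large ones matter.

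**The case against.** The strongest reply is that a condensed article need not print its full baseline table or covariate list; the analysis plan, which is not shown, may hold both. For the model this stands: the Analyses section names no patient covariate, but it does not say that the model is unadjusted. For the baseline comparison it stands only in part, because the article does print a list, and that list does not suit the risk conceded in the Discussion.

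Other points also stand:

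- **Unseen and uncorrected bias.** A reader might infer that selection would go undetected and unadjusted. The document does not support that. The outcome is measured before ACP is delivered, patient characteristics are to be summarised, and repeated-measures analyses are planned. An imbalance could be seen and handled with data already in hand.
- **A concession about prognosis.** A reader might also infer that the protocol admits selection on fitness or stage. It does not. It speaks of openness to ACP. Performance status and stage reflect that only indirectly, and the step from openness to prognosis is a reviewer's inference.
- **A fault in the eligibility range.** Nothing is wrong with admitting WHO 0-3. It only means that there is room for the arms to differ.
- **Tumour type.** The 34/34 quota per hospital largely balances it.
- **Safeguards.** Paired randomisation of comparable hospitals, similar consent information and systematic assessment of all patients lower the risk. They do not remove it: invitation of all eligible patients follows the unblinded judgement of life expectancy, and it does not control who consents.
- **Size.** The imbalances and the 0.5 SD gap are assumed; the document offers no evidence that they will occur.

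**Conclusion.** The point holds in a limited form. The protocol concedes a selection risk specific to intervention hospitals, then names a baseline comparison that contains no prognostic variable and no baseline outcome, although these data will exist for included patients. This is a weakness in what the Analyses section states. It is not proof of bias, and it is not proof that the model lacks adjustment.

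Under the assumptions shown, a 10-point imbalance barely moves the false-positive rate (6.3%). A 20-point imbalance roughly doubles it (10.5%) and produces a bias of one fifth of the target effect. Both figures take the baseline outcome as unused. The conclusion rests on recruitment with the arm known, which is inferred from the lack of blinding and the arm-specific consent information. The change is worth making because it is cheap and the protocol itself raises the risk.

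**What to change.** In the Analyses section:

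1. Extend the baseline comparison of the arms to WHO performance status, disease stage, and baseline emotional functioning and symptoms.
2. Pre-specify a multilevel analysis of the 2.5-month endpoint adjusted for these variables. Tumour type may be added as a covariate, though the quota leaves it little to correct. If the analysis plan already contains such an analysis, a sentence referring to it is enough.
3. From the systematic eligibility assessment promised in the Discussion, tabulate by arm the numbers assessed, excluded for anticipated life expectancy under three months, and eligible but not included. This is the more direct check on selection for openness to ACP, which the clinical variables reach only indirectly.

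Cost: changed wording, a few more covariates in one model, and one extra table. The variables are already determined for eligibility or collected at inclusion, and the counts come from an assessment already promised. Neither the design nor the sample size changes. The sponsor may have to report an imbalance if one appears.
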